### Inclusion and Exclusion Criteria

Individuals between the ages of 18-50 years with reported sleep disturbances were included in the study. Individuals were excluded if they reported or exhibited any health conditions beyond insomnia-related symptoms. Exclusionary criteria were based on one or more of the following considerations: the criterion in question is (1) known to alter sleep, (2) known to substantially increase interparticipant variability, (3) known to put the volunteer outside the range of what is considered healthy, or (4) required by regulation. Detailed inclusion and exclusion criteria are referenced in Textbox 1.

A detailed description of inclusion and exclusion criteria of a pilot randomized controlled trial evaluating the preliminary effectiveness of continuous theta burst stimulation in improving sleep in individuals with reported sleep disturbances.
**Inclusion criteria**
18-50 years oldSelf-reported sleep disturbances on 2 of 3 inventories:Pittsburgh Sleep Quality Index ≥6Insomnia Severity Index ≥15Epworth Sleepiness Scale ≥11
**Exclusion criteria**
Unwillingness to provide informed consentPresence of a metal implant or medical device which poses a safety risk for magnetic resonance imaging or transcranial magnetic stimulationSelf-reported past or present medical diagnosis of sleep- or breathing-related disordersTravel outside the time zone within 1 week prior to the enrollment visit or while active during the studySelf-reported major medical or neurological problemsSelf-reported past or present history of cardiovascular diseaseSelf-reported past or present history or first-degree family history of any seizures or seizure disordersSelf-reported underlying acute or chronic pulmonary diseaseSelf-reported history of fainting spells or syncopeSelf-reported past or present psychiatric problemsSelf-reported suicidal ideationSelf-reported current use of prescription medicationsSelf-reported current use of supplements that affect sleepSelf-reported caffeine use in excess of 300 mg per day on averageSelf-reported regular nicotine useSelf-reported or suspected heavy alcohol indicated on the Alcohol Use Disorders Identification Test (AUDIT) as greater than or equivalent to 14 drinks a week for male individuals and 7 drinks a week for female individualsSelf-reported use of illicit drugsSpeaking English as a nonprimary languageLess than a ninth-grade educationEngaged in overnight shift workFemale individuals only: positive urine pregnancy testFemale individuals only: self-reported current breast-feeding or collecting breast milk

### Study Activities

#### Enrollment and Baseline Assessment (Visit 1)

Eligible participants were invited for an in-person screening and baseline data collection session lasting approximately 2-3 hours. After participant consent was obtained by trained study staff members, the participants underwent a baseline assessment, including measurement of intellectual capacity with the Wechsler Abbreviated Scale of Intelligence by a certified administrator, subjective sleep assessment including the Pittsburgh Sleep Quality Index and Insomnia Severity Index, and other cognitive assessments.

#### At-Home Actigraphy Week

Upon the completion of the enrollment visit, participants were fitted with a wrist actigraphic sleep monitor that they wear for at least 5 days prior to returning for the in-laboratory assessment sessions and continued to wear the device during the intervening washout week between the 2 in-residence laboratory stays. Participants also completed a web-based sleep diary each morning. Throughout the entire period of enrollment, participants were required to maintain a regular sleep schedule and were not permitted to use caffeine products for 48 hours prior to the in-laboratory overnight stays.

#### Overnight In-Residence Laboratory Sessions (Visits 2 and 3)

Participants completed 2 overnight in-residence laboratory stays according to a double-blind counterbalanced crossover design, with each session separated by at least 5 days. Figure 2 provides a graphical overview of the in-residence laboratory activities.

**Figure 2 figure2:**

Timeline of the in-residence laboratory testing for the pilot randomized controlled trial. Participants arrive at the lab at 1500 and undergo cognitive testing followed by a preintervention MRI scan. The intervention is administered between 1900 and 2000 and is randomly assigned as either active cTBS stimulation or an identical appearing sham condition. After stimulation, participants complete a postintervention series of MRI scans, followed by a brief cognitive testing battery. At 2200, they are escorted to the sleep lab and PSG electrodes are applied. Lights out occur at 2300 and the participant is provided with an 8-hour undisturbed period for PSG-monitored sleep. Following wake-up at 0700 the next morning, the participant is provided a light breakfast and completes a final battery of cognitive tests. This procedure is repeated on separate weeks for the active cTBS and placebo conditions. cTBS: continuous theta burst stimulation; MRI: magnetic resonance imaging; PSG: polysomnography.

#### Cognitive Testing Block

Participants arrived at 3 PM and completed approximately 3 hours of cognitive testing with a trained and certified administrator, including the 10-minute psychomotor vigilance testing (PVT) and Karolinska Sleepiness Scale (KSS) at 3 time points separated by an hour, in addition to the Visual Analog Mood Scale, State-Trait Anxiety Inventory-State only (STAI-S), Beck Depression Inventory (BDI-II), California Verbal Learning Task 3 (CVLT3), go/no-go task (GNG), repeatable battery for the assessment of neuropsychological status (RBANS) symbol digit test, RBANS digit span, RBANS story memory test, and Glasgow Content of Thoughts Inventory (GCTI).

#### Prestimulation Neuroimaging

MRI scans were collected on a Siemens MAGNETOM Skyra 3T scanner (Siemens) using a 32-channel head coil. Participants completed a series of scans that included structural (magnetization-prepared rapid gradient-echo), functional (10-min eyes open) resting state, and proton magnetic resonance spectroscopy (^1^H MRS) scans, with voxels placed in (1) the anterior cingulate gyrus and (2) posterior cingulate or precuneus. Functional MRI data will be preprocessed with standard neuroimaging packages, including statistical parametric mapping 12, FSL, and the functional connectivity toolbox (CONN v17f or later; focusing on DMN network connectivity) following standard published pipelines [44].

#### Intervention: cTBS Versus Sham

Following the first MRI scan, participants exited the scanner and underwent either cTBS stimulation or sham stimulation according to their preassigned double-blinded condition. The stimulator was preprogrammed prior to the start of the session and the participants and technicians that administered the stimulation procedure were blind to the administered condition. Each individual was expected to have a different sensitivity to the magnetic fields generated by the stimulation coil, and the stimulation intensity was adjusted based on each individual’s resting motor threshold (RMT). The real-time, motor-evoked potential of muscle contraction is provided to ensure consistent force production. Once the RMT was identified, the stimulation intensity for TBS was set to 70% of each participant’s RMT.

For primary rTMS stimulation, we located a predetermined node in the inferior parietal lobe, localized by coregistering the participant’s head, structural T1-weighted MRI image, and TMS coil in the same space using a TMS 3D Neuronavigation System. Once coregistration was complete, the Neuronavigation system provided real-time feedback on the TMS coil location and recorded the coil position and orientation relative to the head. The cTBS was applied using a figure-of-8 coil with an active cooling system connected to the MagPro magnetic stimulator (MagVenture Cool-B65). The same coil has 2 sides, 1 designed for active TMS stimulation, and the other is equipped with a magnetic shield that effectively blocks any stimulation and is used for the sham condition. The rTMS setup is shown in Figure 3.

For this project, we selected an easily accessible node of the DMN located on the left lateral parietal (LLP) cortex. The exact spatial location for stimulation is based on the Yeo et al [45] probability atlas. We downloaded this atlas into the Mango 4.1 visualization program (and identified the centroid of the LLP node of the DMN at the MNI coordinates of x (–48), y (–61.5), and z (32.5). These coordinates are converted into the same stereotaxic space as the participant’s brain to allow precision localization of the LLP node as the target for stimulation. Once this site was localized for the participants, a 40-second cTBS stimulation train (600 stimuli/session) or identically matched sham stimulation was administered using a MagVenture MagPro X100 stimulator (MagVenture Inc) connected with a figure-of-8 magnetic coil with active cooling.

**Figure 3 figure3:**
[figure not shown]
Transcranial magnetic intervention system set-up for the pilot randomized controlled trial. Left: (A) the continuous theta burst stimulation is administered with a MagVenture Cool-B65 stimulator that included an active and sham side; (B) the resting motor threshold was determined using a MagPro X100 stimulator with a figure-of-8 coil; (C) the transcranial magnetic stimulation system is maintained at a constant temperature using an active cooling system. Middle: the stimulation is directed by a computerized system that detected the orientation of the head in space using (D) an antenna camera and correlate it with the individual’s coregistered magnetic resonance imaging scan. Right: An image showing the Neuronavigation system used to administer the transcranial magnetic stimulation to the precise default mode network locations.

#### Poststimulation Neuroimaging

Immediately following the cTBS or sham stimulation period, each participant underwent a second neuroimaging session that was identical to the prestimulation MRI session previously described.

#### PSG Recording

Participants slept undisturbed in a light- and temperature-controlled private bedroom while continuously monitored by a trained technician with a Nihon Kohden JE-921 PSG recording system using standard 10-20 electrode placement. Data from PSG were scored using Polysmith software according to the standard Rechtschaffen and Kales approach by a trained and certified sleep technician who was blind to the participant’s condition and status. The primary outcome metrics include sleep onset latency (SOL), latency to N1, N2, N3, and REM, total sleep time (TST), sleep efficiency (SE), wake after sleep onset (WASO), and number of awakenings and arousals, as well as time and percentage of time spent in each sleep stage.

#### Monitoring

Participants were assessed both prior to stimulation and after receiving stimulation for any adverse somatic, cognitive, or physical symptoms. Any presence of symptoms was logged in a HIPAA-compliant server and the participant was assessed by the study physician to determine if enrollment needed to be discontinued. All adverse events were reported to both IRB and OHRO. All study activity was subject to independent, random auditing from the Department of Psychiatry at the University of Arizona and study sponsors.

#### Data Management

All collected data were deidentified and stored within HIPAA-compliant, password-protected servers immediately after collection. Study data were only accessible to IRB-approved study staff. All data were checked and double-entered by study personnel no more than 1 week after data collection. Data quality checks were conducted every quarter by staff members for additional data assurance. Any data collected after participants’ consent were included in the study database for both compliant and noncompliant participants. However, following a per-protocol analysis, we are only using data from participants who fully completed the study due to within-subjects analysis.

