### Study Design and Randomization

This phase 1 clinical trial (ClinicalTrials.gov NCT04953559) will be conducted with a randomized, double-blind, sham-controlled, counterbalanced, crossover design. Participants serve as their own controls as they undergo 2 identical study sessions separated by at least 5 days (ie, washout period). Participants and study personnel who interact with the participants will be blind to the specific condition (active cTBS vs sham) the participant receives during each study visit. Using a prespecified, equally balanced, block randomization procedure, participants will be assigned to the order in which they receive active cTBS and sham stimulation conditions. The randomization list will be generated by a computer random number generator, with the constraint that half of the participants of each biological sex will receive sham first and half will receive the active cTBS first. This design will allow us to examine the intraindividual effects of the active cTBS and establish the superiority of active cTBS compared with sham stimulation in improving PSG sleep outcomes.

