**Figure 1 figure1:**
[figure not shown]
Overview of the pilot randomized controlled trial study design. Participants first complete a web-based eligibility survey screening for sleep disturbances. Potentially eligible volunteers complete an in-lab enrollment process and baseline assessment (visit 1) at a large Southwestern University medical research center. Participants are then randomized to a stimulation order condition. After at least 5 days with actigraphically measured sleep, participants return for an 18-hour overnight session involving 2 MRI scans and overnight sleep (visit 2) at the medical research center. Depending on their condition assignment order, they either receive active cTBS or sham intervention. Participants then undergo a washout period of at least 5 days that includes actigraphically measured sleep. They then return for an identical overnight visit that involves the alternate intervention condition. cTBS: continuous theta burst stimulation; MRI: magnetic resonance imaging.

**Table 1 table1:** List of study activities and assessments performed during study visits during a pilot randomized controlled trial evaluating the preliminary effectiveness of continuous theta burst stimulation in improving sleep in individuals with reported sleep disturbances.

Study activities and assessments			Baseline screening and enrollment (visit 1)		At home		Overnight visits (visits 2 and 3)

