### Participants and Recruitment

A total of 20 otherwise healthy adults with self-reported sleep disturbances were recruited from the greater Tucson and Phoenix metropolitan areas. Recruitment strategies include flyers posted on community boards, advertisements in local newspapers, sponsored social media posts, and email lists at local universities. Individuals who were recruited from the community were directed to complete a web-based survey in a HIPAA (Health Insurance Portability and Accountability Act)–compliant server. If participants met the initial inclusion criteria, a study member then completed a preliminary phone screening with the participant. Study personnel then scheduled an in-person screening visit for eligible individuals.

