### Power Analyses

During the study design, we conducted a power analysis to determine the sample size necessary to compare mean changes in DMN connectivity before and after cTBS using a within-subjects ANOVA approach. From prior cited work on transcranial magnetic stimulation (TMS) and FC, a total sample of 20 was found to have sufficient power to answer the research questions to include analysis of 2 groups (within-subject active and sham), 2 repeated measurements (before and after TMS), and a correlation between the change in DMN activation and sleep outcome metrics [42,43].

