## Results

Our study was funded in September 2020 by the Department of Defense (W81XWH2010173). We completed the enrollment of our target population of 20 participants in October 2022. As of July 2023, we will initiate extensive neuroimaging data analysis and anticipate that the full results of the study will be published by 2024.

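### The completers-only rule is not required by the within-subjects design, and it allows exclusions after randomisation that may be related to treatment, including from the side-effect comparison

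*Protocol article*

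**What the plan says.** Data Management states that data gathered after consent "were included in the study database for both compliant and noncompliant participants". It then limits what is analysed: "following a per-protocol analysis, we are only using data from participants who fully completed the study due to within-subjects analysis". The restriction carries no exception by outcome, the article does not define full completion, and it describes no all-randomised or all-available-data analysis elsewhere.

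The surrounding sections fix the context:

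- **Randomisation.** The Figure 1 caption places it after visit 1 and before the actigraphy period and both overnight stays: "Participants are then randomized to a stimulation order condition". Study Design and Randomization balances order within sex, so that "half of the participants of each biological sex will receive sham first and half will receive the active cTBS first".
- **Discontinuation.** Under Monitoring, symptoms are checked before and after stimulation, and the study physician then decides whether the participant continues.
- **Side effects.** Exploratory Analysis lists them, with cognition and mood, among the outcomes compared between active and sham.
- **Sample size.** Power Analyses says that "a total sample of 20 was found to have sufficient power to answer the research questions". Participants and Recruitment and the Results section both give 20 as the number recruited or enrolled ("We completed the enrollment of our target population of 20 participants in October 2022"). No allowance for dropout is stated.

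**The concern.** The stated reason does not lead to the stated rule. A within-subject contrast for functional connectivity (FC) needs the four FC scans. It does not need both polysomnography (PSG) nights, the actigraphy weeks or every cognitive block. A participant with all four scans and one failed PSG night has complete information on FC, yet on a literal reading is dropped from that analysis too.

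Who is excluded is settled after randomisation and, for some, after stimulation. Someone stopped for symptoms after active stimulation at the first overnight visit would leave every comparison, including the side-effect comparison where that experience matters most. The article aims to establish superiority of active over sham, and such a claim is weaker if it rests on a subset chosen by events that treatment can influence.

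Two further consequences depend on there being non-completers. The analysed number would fall below the 20 used for power, and the planned balance of order within sex could be disturbed.

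**Working it through.** **1. Does the reason require the rule?** Set the analyses beside the data each one needs:

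| Analysis (section) | Data needed from one participant |
|---|---|
| FC, active v sham, pre v post (FC Changes to the DMN) | four FC scans |
| PSG, active v sham (PSG Analysis) | two PSG nights |
| Cognition, mood (Exploratory Analysis) | that measure at both visits |
| Side effects (Exploratory Analysis) | stimulated at least once |

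No row needs completion of the whole study. The last row does not even need both visits.

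**2. Can exclusion be related to treatment?** The order of events is visit 1, randomisation, actigraphy, first stimulation, symptom check with possible discontinuation, washout, second stimulation. At least one exit route lies after stimulation and is triggered by symptoms, so the answer is yes in principle. The article does not say whether it happened.

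**3. The plan's own figure.** The sample of 20 cannot be reproduced. The article gives no alpha, sidedness, target power, effect size, standard deviation or within-subject correlation. What follows is conditional on assumed values.

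**4. Illustration: cost of a smaller n.** Assume a paired contrast, two-sided alpha 0.05 and standardised effect dz = mean paired difference / SD of paired differences. Power = P(|T| > t(0.975, n−1)), where T is noncentral t with n−1 degrees of freedom and noncentrality dz·√n.

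| n analysed | if 20 gives 80% (dz 0.660) | if 20 gives 90% (dz 0.764) |
|---|---|---|
| 20 | 80.0% | 90.0% |
| 19 | 77.7% | 88.3% |
| 18 | 75.2% | 86.3% |
| 16 | 69.5% | 81.5% |

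From the 80% baseline, each loss costs about 2 to 3 points: (80.0 − 69.5)/4 = 2.6.

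**5. How much of that does the rule itself cause?** Let n_c participants complete and m have the first overnight visit only, split equally between orders, with within-subject correlation ρ. In a 2×2 crossover with period and treatment effects, a completer carries treatment information 1/[2(1−ρ)] and a one-visit participant 1/4 (in units of 1/variance). Dividing gives

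effective n = n_c + m(1−ρ)/2.

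- m = 2, ρ = 0.2: 18 + 2(0.8)/2 = 18.8. With ρ = 0.7: 18 + 2(0.3)/2 = 18.3.
- m = 4, ρ = 0.2: 16 + 4(0.8)/2 = 17.6. With ρ = 0.7: 16 + 4(0.3)/2 = 16.6.

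With a sequence term as well, effective n = n_c / [1 − (1−ρ)m/(2·20)]. For m = 2 this gives 18/0.96 = 18.75 to 18/0.985 = 18.27; for m = 4, 16/0.92 = 17.4 to 16/0.97 = 16.5. A mixed model therefore recovers only a minority of what one-visit participants cost. A participant complete on the outcome concerned but missing something else is recovered in full by deciding inclusion per outcome.

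**6. Order balance.** Suppose orders of 10 and 10 become 10 and 7. With treatment effect τ and visit effect π, the plain mean of paired differences is [10(τ+π) + 7(τ−π)]/17 = τ + (3/17)π, so 18% of any visit effect enters the estimate. With a period term in the model the leak is zero, whether or not the analysis is restricted to completers.

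**The case against.** The strongest reply is that nothing in the article shows anyone was lost. The numbers given are enrolment counts, and no completer count appears. The remark about noncompliant participants covers data from consent onwards, and consent precedes randomisation, so those people need not have been randomised. This stands. A reader might infer that the analysed number is already below 20 and that the sex-by-order balance is broken; the article supports neither.

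It is also fair to say that the power table shows the cost of dropout rather than of the rule, and that its inputs are assumed. Step 5 confirms that a mixed model restores little for one-visit participants, so it would be too strong to say that the rule throws away much precision. The leak in step 6 is a matter of the missing period term, not of the completer restriction; the PSG section mentions covariates without listing them, which an article may do.

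Full completion could simply mean both overnight visits done. That is a reasonable reading, and it would save participants who miss only an actigraphy week. It would still exclude someone discontinued after the first stimulation.

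Each completer contributes both conditions, so unequal arms of the parallel-group kind do not arise, and bias requires non-completion related to the outcome. That limits the concern without removing it. Adverse events were also reported to the oversight bodies, so safety oversight is not lost; what suffers is the active-versus-sham comparison of side effects.

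Finally, this is a small pilot, and supporting analyses may sit in a fuller document. But the article does not leave the analysis population open: it states a rule and a reason, and the reason does not support the rule.

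**Conclusion.** The point holds as a fault in a stated rule. The completers-only restriction is unqualified, rests on a reason that does not require it, permits exclusions after randomisation and after stimulation, and, read literally, takes out of the side-effect comparison anyone stopped because of side effects.

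Its size in this trial cannot be derived. With no non-completers the analysed number is 20 and nothing is lost. With two or four, power would fall from an assumed 80% to about 75% or 69%, under a two-sided 5% paired test calibrated to 80% at 20. Most of that fall would occur under any analysis if the missing participants had only one visit. The main exposure is selection bias and incomplete side-effect reporting, neither of which the article allows one to quantify. The rule should be changed, and the change is cheap.

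**What to change.** - **Inclusion per outcome.** Keep a participant who has the outcome concerned at both visits, even if another component is missing.
- **Scalar outcomes** (PSG measures, region-level FC, cognition, mood). Analyse all randomised participants with available post-stimulation data, as randomised, in a mixed model with treatment, period, sequence and a random participant effect.
- **Voxelwise analyses in CONN.** Include everyone with the four FC scans. It has not been shown that a mixed model with missing visits fits that pipeline, so none is asked for there.
- **Side effects.** Report them for everyone stimulated, by the condition received.
- **Sensitivity and reporting.** Keep the completers-only result as a sensitivity analysis with full completion defined, and report the number of exclusions with reasons, by order and condition.

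The cost is revised wording, a missing-at-random assumption for the mixed model and a little more analysis work. No new data are needed, since the article says they are already "included in the study database for both compliant and noncompliant participants". If everyone completed with all components present, no participant would be added and the sensitivity analysis would cover the same 20 people.
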